### 2.7. Randomization and grouping

A stratified random method will be adopted in the experiment with centers as the stratified factor. A total of 673 patients who fulfilled the criteria will be randomized into the NXT, BYHW, YYTN, and placebo groups in a 2:1:1:1 ratio. Randomized numbers will be generated by independent statisticians using SAS9.4 software (Beijing Hospital of TCM Version. Order number: 9C1XJD). Randomized numbers, rank sequences, and groupings will then be stored in opaque envelopes maintained by designers and statisticians throughout the study. All envelopes will be given running serial numbers, and each patient received one. Patients will be allocated to different groups according to the contents of the envelopes. Each participant received treatment assigned according to the randomization list. All clinical personnel and outcome assessors will be blinded to the intervention.

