### 2.10. Outcome evaluation

#### 2.10.1. Primary outcomes.

The primary outcome of this study is HF incidence. These data will be recorded over 180 days.

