#### 2.10.2. Secondary outcomes.

Recurrence rates of other major adverse cardiovascular events, such as AMI, all-cause mortality, readmission rate due to cardiovascular events, non-fatal stroke, non-fatal AMI, and cardiovascular death, will be recorded by outpatient and telephone follow-up within 180 days.The Seattle Angina Questionnaire score and 6-minute walk test results will be evaluated at baseline and on days 30, 90, and 180.Echocardiography and carotid ultrasonography will be performed by the same physician at baseline and on days 90, and 180.Biological indicators: cardiac troponin I, creatine kinase isoenzyme-MB, total cholesterol, triglyceride, low-density lipoprotein cholesterol, apolipoprotein A1, apolipoprotein B, D-dimer, prothrombin time, activated partial thromboplastin time, thrombin time, fibrinogen, international standardized ratio, platelets, and immunoglobulin G will be assessed at baseline and on days 90 and 180.

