### 2.12. Sample size

The sample size estimation was based on a superior efficiency comparison between the 2 groups of rates. The following formula was used for estimation:

$$\begin{array}{l} n_{T}+n_{C}=(\frac{n_{T}\pi_{T}+n_{C}\pi_{C}}{n_{T}+n_{C}})(1-\frac{n_{T}\pi_{T}+n_{C}\pi_{C}}{n_{T}+n_{C}}){\left[\frac{\mu_{1-\alpha }+\mu_{1-\beta }}{\pi_{T}-\pi_{C}}\right]}^{2} \end{array}$$

$n_{T}$ and $n_{C}$ are the sample sizes for the treatment and control, respectively; α is the test level; β is the type-II error; 1-β is the power; and μ is the standard normal deviation threshold (μ1-α and μ1-β represent the corresponding one-sided bounds of 1-α and 1-β, respectively).

Assuming that the sample size ratio between the treatment and control groups is *r*, the above sample size formula is reduced to

$$\begin{array}{l} n_{T}=(\frac{\pi_{T}+\pi_{C}/r\;}{1+1/r\;})(1-\frac{\pi_{T}+\pi_{C}/r\;}{1/r\;}){\left[\frac{\mu_{1-\alpha }+\mu_{1-\beta }}{\pi_{T}-\pi_{C}}\right]}^{2} \end{array}$$

If π_T_ and π_C_ are the endpoints of observation of the efficacy of secondary prevention of myocardial infarction in the NXT and control groups, the incidence of endpoints was 5.6% and 15.4%, respectively. The Bonferroni adjustment was used to adjust α, α = 0.05/6 (unilateral), and β = 0.2. The NXT group consisted of 261 patients.

If π_T_ and π_C_ are the total response rates of myocardial infarction in the BYHW and control groups, respectively, the total effective rates were 92.30% and 76.92%, respectively. The BYHW group consisted of 146 patients.

If π_T_ and π_C_ are the total response rates of myocardial infarction in the YYTN and control groups, respectively, the total effective rates were 93.88% and 78.43%, respectively. The YYTN group consisted of 133 patients.

According to the Drug Registration Administration Measures and considering factors such as falling off, 673 patients are required.

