### 2.13. Statistical analysis

Relevant logic verification will be conducted to determine the causes of participants’ falling off and missing data.

Statistical analysis will be performed using SPSS 15.0 (PN:32119001, SN:5045602) by a third party that has no access to the blinding codes. Continuous data will be expressed as mean ± standard deviation. Categorical variables will be expressed as frequencies (%). Continuous variables between the groups will be compared using the *t* test for normally distributed values. A completely randomized design and one-way analysis of variance will be used to compare normally distributed continuous variables with homogeneity of variance between groups, a completely randomized design and one-way analysis of variance will be used. The SNK-q test will be used for pairwise comparisons between groups. The rank-sum test will be used to compare non-normally distributed continuous variables between groups. Comparisons between groups will be performed using the chi-square test (or Fisher’s exact test when the expected frequency is <5). Post hoc analysis was performed using LOGISTIC and COX regression analyses. All calculations will be performed using SPSS 15.0. The threshold for significance will be set to *P* < .05 (2-tailed).

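### The primary heart-failure comparison is a valid but unadjusted chi-square test that leaves the baseline echocardiogram unused; pre-specified adjustment would recover a modest amount of power at little cost

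*Protocol article*

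**What the plan says.** - Section 2.10.1: "The primary outcome of this study is HF incidence", counted over 180 days. This is a yes/no outcome for each patient.
- Section 2.13, for categorical data: "Comparisons between groups will be performed using the chi-square test", with Fisher's exact test as the small-count fallback. The sentence does not name HF. However, the other tests listed there (t test, analysis of variance, SNK-q, rank-sum) do not fit a proportion.
- Section 2.13, on regression: "Post hoc analysis was performed using LOGISTIC and COX regression analyses". No covariates are named.
- Section 2.10.2: "Echocardiography and carotid ultrasonography will be performed by the same physician at baseline and on days 90, and 180". Section 2.4 places entry two weeks after reperfusion, so cardiac imaging is scheduled just before the period in which HF is counted.
- Section 2.7: "A stratified random method will be adopted in the experiment with centers as the stratified factor". Centre is the only stratification factor, so cardiac function is not balanced by design either.

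**The concern.** Of the baseline measurements listed, the echocardiogram is the one most directly related to HF. The stated confirmatory test cannot use it, and the only methods that could are given a post hoc role. If baseline left ventricular function predicts HF, an unadjusted test treats that predictable variation as noise. A pre-specified adjusted test would then have more power from the same patients and visits.

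Power is the thing at stake, particularly for the two granule arms, where about 135 patients face about 135 on placebo. A second, smaller cost is interpretive: with regression labelled post hoc, an adjusted result would carry less weight than one fixed in advance.

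**Working it through.** **Inputs.** The total is 673, "randomized into the NXT, BYHW, YYTN, and placebo groups in a 2:1:1:1 ratio" (section 2.7). One fifth is 673/5 = 134.6, so the arms are about 269 for NXT and 135 for each other arm. For the planning rates, NXT versus control, "the incidence of endpoints was 5.6% and 15.4%, respectively" (section 2.12). The introduction gives HF incidence after AMI as 16.7%. The analysis level is two-sided 0.05 (section 2.13).

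Assumptions, because the document does not supply them:
- Either pair of rates applies to 180-day HF: 15.4% vs 5.6%, or 16.7% halved to 8.35%.
- The same pairs apply to the granule arms, which section 2.12 sizes on response rates instead.
- The covariate has the prognostic strengths shown below.

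**1. The plan's own figure.** Take r = 2, one-sided alpha 0.05/6, power 0.80 and n_T = (1+r)·p̄(1−p̄)·[(z₁₋α + z₁₋β)/(π_T − π_C)]².

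p̄ = (2×0.056 + 0.154)/3 = 0.0887, so p̄(1−p̄) = 0.0808. The bracket is (2.394 + 0.842)/0.098 = 33.02, squared 1,090. Then n_T = 3 × 0.0808 × 1,090 ≈ 264, against the stated 261. (The reduced formula as printed gives 71, so the figure needs the (1+r) form.) The planning is thus for an unadjusted comparison of two proportions, like the stated test.

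**2. Unadjusted power.** Power = Φ[(Δ − 1.96·se₀)/se₁], with se₀ pooled, se₁ unpooled and Δ = 0.098.
- NXT, 269 vs 135: se₀ = 0.0300, se₁ = 0.0341, so Φ(1.15) ≈ 0.88.
- Granule arm, 135 vs 135: se₀ = 0.0373, se₁ = 0.0368, so power ≈ 0.75.

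**3. Adding one baseline covariate.** The simulation model is logit P(HF) = a + b·x + d·arm with x standard normal; a and d are solved so that the marginal rates stay fixed. Entries are power in % for Pearson chi-square → likelihood-ratio test for arm in the adjusted logistic model, at two-sided 0.05. There are 2,500 trials per cell (8,000 for the two entries marked *), with simulation error of about 1 point.

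| Slope b per SD (c-statistic) | Granule, 16.7% halved | Granule, 15.4% vs 5.6% | NXT, 16.7% halved | NXT, 15.4% vs 5.6% |
|---|---|---|---|---|
| 0.5 (about 0.63) | 55→57 | 77→78 | 70→71 | 88.8→88.5* |
| 0.8 (about 0.71) | 55→59 | 78→81 | 69→70 | 89.1→89.8* |
| 1.0 (about 0.75) | 54→59 | 77→81 | 71→73 | 88→91 |
| 1.3 (about 0.80) | 57→64 | 76→82 | 70→75 | 89→93 |
| 1.6 (about 0.83) | 56→67 | 77→86 | 70→78 | 89→94 |

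At two-sided 0.0167, which matches the planning level of one-sided 0.05/6, the granule comparison at 16.7% halved goes 38→42, 39→47 and 38→49 at slopes 1.0, 1.3 and 1.6.

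**4. Type I error.** With 15.4% in both arms and nominal 0.05, rejection was 0.042–0.061 for chi-square and 0.046–0.062 for the adjusted test. A repeat run of the adjusted test gave 0.046–0.057.

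**5. Does the gain carry over to a risk-difference interval?** Not for NXT unless the covariate is strong. The table shows how often the test rejects, or how often the Wald interval for the standardised risk difference excludes zero (3,000 trials per cell, two-sided 0.05).

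| Slope | 15.4% vs 5.6%: chi-square, interval | 16.7% halved: chi-square, interval |
|---|---|---|
| 0.5 | 0.891, 0.865 | 0.704, 0.657 |
| 0.7 | 0.888, 0.868 | 0.694, 0.675 |
| 1.0 | 0.884, 0.889 | 0.696, 0.686 |
| 1.6 | 0.892, 0.925 | 0.689, 0.758 |

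The main reason is visible in step 2: at 2:1 the unpooled standard error (0.0341) exceeds the pooled one (0.0300). The granule arms do gain with this interval: about 1–2, 2–4 and 4–6 points at slopes 0.5, 0.7 and 1.0.

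**The case against.** The strongest reply is that nothing here is wrong. A chi-square test on a randomised binary outcome controls type I error, and chance imbalance in cardiac function is already covered by that error rate. That stands: a reader might infer bias or invalidity, and step 4 shows neither.

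Second, the chi-square sentence is generic, and covariate choice is commonly left to the SAP. This stands only in part. The article does not leave regression open; it assigns it a post hoc role and states one test for proportions. That is a stated choice, although the wording is loose.

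Third, the covariate and its strength are not in the document. Section 2.10.2 says echocardiography and names no parameter, so ejection fraction cannot be presumed to be recorded. This stands, and it is why only a range can be given.

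Fourth, a reader might apply a conventional correlation of 0.5 between covariate and outcome and claim 7 to 12 points throughout. Under the same logistic model, that correlation needs a c-statistic of about 0.88 at 15.4% incidence and about 0.91 at 12.5%. Nothing in the document supports such strength, so those figures should not be used.

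Fifth, an adjusted risk-difference interval used as the test could do worse than chi-square for NXT. Step 5 confirms this, and it determines how the fix must be written.

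**Conclusion.** The point holds as a missed efficiency. The stated confirmatory analysis of 180-day HF is valid but leaves a scheduled baseline measurement unused.

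Across the simulation runs at two-sided 0.05, and subject to the assumed rates and covariate strength, the gain from an adjusted likelihood-ratio test is:
- each granule arm versus placebo: about 2 points (weak covariate, slope 0.5), 4–5 points (c-statistic about 0.75) and 8–12 points (about 0.83);
- NXT versus placebo: about 0, 2–3 and 4–9 points at the same strengths.

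Type I error does not change. The granule arms start from the lower power and gain most; NXT gains essentially nothing if the covariate is weak. The documents do not support saying that the chi-square result would be biased, that the trial would fail without adjustment, or that any adjusted estimate automatically brings more power.

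**What to change.** In section 2.13, before unblinding:

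1. Pre-specify the primary analysis as a logistic regression of 180-day HF on treatment arm and one continuous baseline echocardiographic measure of left ventricular function (ejection fraction, if that is what is recorded).
2. Base the primary test of each drug versus placebo on that model's likelihood-ratio test.
3. Report the standardised risk difference with its confidence interval as the effect estimate, not as the test, so that the result still refers to HF incidence.
4. Impute a missing baseline value from baseline data only, so that no patient is dropped for a missing covariate.
5. Keep chi-square/Fisher as a supportive analysis and remove the post hoc label from this model.

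No new patients, visits or measurements are needed, and logistic regression is already among the listed methods. The costs are small: the covariate and the missing-value rule must be fixed in advance, and the risk difference needs a short extra calculation, possibly outside SPSS 15.0, the only analysis software section 2.13 allows for. Whether to adjust for centre is a separate question.

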### 2.14. Data management and quality control

All data will be obtained from the follow-up subjects. The data monitoring committee is composed of experts with relevant professional knowledge and experience. The data monitoring committee will regularly review the data accumulated in this study, track the progress of the project, collect the problems existing in the implementation of the project, and provide timely feedback to the project leader. The purpose is to protect the safety of the subjects and to ensure the reliability and effectiveness of the test. The investigators will maintain all trial data, including the confirmation of all participants, original informed consent forms, case report forms, and detailed records of drug distribution/recall. The subjects’ personal information will not be disclosed unless required by applicable law. Subject to confidentiality, the inspectors, ethics committee, research supervision, and management personnel have access to the original records of the subjects to verify the trial process and data. Except when permitted by the regulation, records of participants’ participation in the trials shall be kept confidential and shall not be made public. The data will be processed anonymously, omitting information that can identify the individual subjects. The trial data will be retained by the investigators. If the results of the trial will be published, the identity information of the participants would remain confidential.

## 3. Discussion

AMI is a serious threat to human health. Although reperfusion therapy is widely performed, heart failure, cardiogenic shock, arrhythmia, recurrent myocardial infarction, and rehospitalization after myocardial infarction still seriously affect the quality of life of patients and cause a huge economic burden to society. Therefore, it is important to reduce the occurrence of adverse events and improve patients’ quality of life.

TCM has a history of >2000 years of treatment for AMI. The TQAB method can improve cardiac function, slow myocardial remodeling, and improve the quality of life of patients.

We investigated the TCM treatment of 5000 AMI inpatients from 2000 to 2008 and found that TCM was helpful in improving the quality of life of AMI patients.^[20]^ Another clinical study has confirmed this conclusion.^[21]^

However, the effect of TQAB on the long-term prognosis of patients after myocardial infarction reperfusion requires high-quality evidence. Whether there are differences in the efficacy of different components of TQAB drugs requires further research.

Therefore, we adopted a prospective, multicenter, randomized controlled, double-blind, double-dummy method to observe the efficacy of TQAB with different components on the incidence of heart failure and quality of life after AMI reperfusion. To verify the scientific and universal applicability of TQAB in the treatment of AMI. Optimizing the treatment scheme of integrated traditional Chinese and western medicine for myocardial infarction after reperfusion. We are looking forward that the result of this study will provide a scientific basis for the clinical application of TQAB.
